# Electrical Dry Needling and Therapeutic Exercise Versus Therapeutic Exercise in Patients With Chronic Nonspecific Neck Pain: Protocol for a Randomized Controlled Trial

**DOI:** 10.2196/91491

**Published:** 2026-08-20

**Keywords:** chronic neck pain, therapeutic exercise, electrical dry needling, randomized controlled trial, musculoskeletal disorders, physiotherapy

## Abstract

**Background:**

Chronic nonspecific neck pain (CNSNP) is one of the most prevalent musculoskeletal disorders worldwide. Its etiology is multifactorial, and it constitutes a leading cause of work absenteeism and a significant socioeconomic burden. Therapeutic exercise, strongly supported by scientific evidence, is considered the cornerstone physiotherapy intervention for its management. In recent years, electrical dry needling (EDN) has been increasingly applied in musculoskeletal disorders with the aim of modulating pain and improving function.

**Objective:**

This protocol aims to compare the effectiveness of EDN combined with therapeutic exercise versus therapeutic exercise alone in patients with CNSNP.

**Methods:**

A randomized, controlled, examiner-blinded clinical trial with 2 parallel intervention arms will be conducted with 70 participants diagnosed with CNSNP, recruited from the outpatient physical therapy department of the University of Almería. Participants will be randomly allocated (1:1) into 2 groups: the experimental group will receive EDN combined with therapeutic exercise (n=35), while the control group will undergo a program of therapeutic exercise alone (n=35). Both groups will receive 1 session per week for 6 weeks (6 sessions in total). Primary and secondary outcome measures will include cervical disability, pain intensity, sleep quality, health-related quality of life, kinesiophobia, pain catastrophizing, cervical range of motion, pressure pain threshold at myofascial trigger points, and cervical muscle endurance. Assessments will be performed at 3 time points: baseline, postintervention, and 2-month follow-up.

**Results:**

This study was funded in 2023. Participant recruitment was conducted between November and December 2025. As of January 2026, 35 of the planned 70 participants had been recruited. Data collection is expected to be completed by March 2026. Data analysis and manuscript preparation will be carried out during 2026, with results anticipated to be published in late 2026.

**Conclusions:**

This trial will provide evidence on the effectiveness of combining EDN with therapeutic exercise in CNSNP, potentially informing clinical practice and improving patient outcomes.

## Introduction

Neck pain is the second most common musculoskeletal disorder after low back pain [1] and represents a significant public health problem [2]. It is defined as pain located between the superior nuchal line and the first thoracic vertebra, which may radiate to the head, trunk, or upper limbs [3]. Clinical manifestations include headaches, sleep disturbances, functional limitations, and negative impacts on activities of daily living, with an increased risk of falls.

Neck pain can be classified by duration: acute (<6 wk), subacute (6 wk to 3 mo), and chronic (>3 mo). Regarding etiology, it can be classified as mechanical, neuropathic, or mixed [4]. The most common form is chronic nonspecific neck pain (CNSNP), characterized by persistent pain lasting more than 3 months without an identifiable specific cause [4,5]. Common triggers include sustained postures, stress, degenerative changes, and multifactorial physical and psychosocial factors. Psychosocial factors, such as high work demands, anxiety, or depression, play a key role in the chronification of symptoms [6,7]. Due to its multifactorial nature, CNSNP poses a significant diagnostic and therapeutic challenge.

The global prevalence of neck pain ranges from 15% to 50%, with a mean of 37% [8]. Approximately half of the world’s population will experience a clinically significant episode during their lifetime, with a projected increase of 30% by 2050 due to aging and changes in work environments [8,9]. Incidence is higher in middle-aged women, particularly those with sedentary lifestyles [4,9]. In Spain, the prevalence is 9.6% in men and 22.8% in women, making it one of the leading causes of referral to physiotherapy [10]. The economic burden is substantial, including both direct costs (consultations, diagnostic tests, and medications) and indirect costs (absenteeism, disability, and lost productivity), reaching thousands of euros per patient per year in some European countries [11,12].

From a pathophysiological perspective, various hypotheses have been proposed. The “Motor Unit Rotation Recruitment Model” suggests that motor units are activated in a rotatory manner to prevent fatigue. However, factors such as stress, sustained postures, or muscle weakness can disrupt this mechanism, leading to overload, metabolic stress, nociceptive activation, and the development of myofascial trigger points (MTrPs) [10,13,14].

Clinical guidelines recommend therapeutic exercise as the first-line treatment for CNSNP in the short and medium term [13,15,16]. Therapeutic exercise has been shown to improve function, reduce pain, and provide a high cost-benefit ratio with minimal adverse effects [17-19]. Its benefits are explained by exercise-induced hypoalgesia, mediated through central and peripheral mechanisms, and by the reduction of kinesiophobia [20-22]. Commonly studied modalities include progressive cervical strengthening programs, yoga, and combined flexor-extensor exercises [17-19]. However, global exercise interventions appear to provide only short-term generalized analgesia.

In parallel, invasive techniques such as electrical dry needling (EDN) have been developed. EDN involves the insertion of a needle into MTrPs, often combined with low-frequency electrical stimulation [23,24]. This technique aims to induce a local mechanical and microtraumatic response, optimize endogenous opioid release, decrease cortisol levels, improve microcirculation, and reduce proinflammatory mediators [23,25]. These effects may contribute to improved motor control and pain reduction.

Although multiple systematic reviews support the effectiveness of therapeutic exercise in CNSNP [26,27], comparative evidence between exercise and emerging invasive techniques remains limited.

## Methods

### Study Design

The present clinical trial is justified, with the primary objective of comparing the effectiveness of EDN combined with therapeutic exercise versus therapeutic exercise alone in patients with CNSNP, evaluating its impact on disability, pain, strength, cervical range of motion, quality of life, and sleep.

This study will be conducted as a randomized, controlled, parallel-group, single-blind clinical trial (assessor-blinded), with two intervention arms: (1) EDN combined with therapeutic exercise and (2) therapeutic exercise alone in patients with CNSNP. Participants will be randomly assigned to 1 of the 2 groups in a 1:1 ratio.

This protocol has been developed in accordance with the SPIRIT (Standard Protocol Items: Recommendations for Interventional Trials) guidelines (Checklist 1). The study will be conducted at the Clinical Unit of the Faculty of Health Sciences, University of Almería, Spain. A SPIRIT flow diagram and a structured schedule of enrollment, interventions, and assessments have been included to improve methodological transparency and reproducibility.

### Ethical Considerations

This study was approved by the Research Ethics Committee of the University of Almería under reference number AP-0429‐2023-C4-F2 and was prospectively registered at ClinicalTrials.gov under identifier NCT06522893. The study will be conducted in accordance with the ethical standards of the Declaration of Helsinki (World Medical Association). All participants will receive verbal and written information about the study and will provide written informed consent before participation. The manuscript does not include an individual's data in any form (including individual images, videos, or identifiable personal details).

### Participants

A total of 70 patients aged 30 to 68 years with CNSNP of more than 3 months’ duration, who are not currently receiving other treatments, will be recruited. Participants will be recruited from internal and external populations associated with the University of Almería through flyers, emails, and informational posters. Interested individuals will contact a researcher via email or telephone, who will schedule an in-person appointment at the outpatient clinical unit affiliated with the Faculty of Health Sciences.

During this initial visit, a physiotherapist blinded to treatment allocation will assess the eligibility of participants according to the inclusion and exclusion criteria. Following this assessment, patients will be randomly assigned to 1 of 2 groups and will receive the corresponding intervention from 2 trained investigators skilled in the study techniques. All participants will provide written informed consent in accordance with the Declaration of Helsinki (World Health Organization; see Figure 1).

**Figure 1. F1:**
[figure not shown]
Schedule of participants and intervention characteristics. CROM: cervical range of motion; MTrPs: myofascial trigger points; NDI: Neck Disability Index; PCS: Pain Catastrophizing Scale; PSQI: Pittsburgh Sleep Quality Index; SF-36: Short Form-36 Health Survey; TSK: Tampa Scale of Kinesiophobia; VAS: Visual Analog Scale.

To improve treatment fidelity and intervention standardization, all physiotherapists involved in the study will receive prior training regarding intervention delivery, outcome assessment procedures, and adverse event reporting. Standardized treatment records and session checklists will be used throughout the study.

Participants were not directly involved in the design or conduct of this trial. However, feedback regarding feasibility, acceptability, treatment burden, and participant satisfaction will be collected during follow-up visits to inform future clinical research and implementation strategies.

To ensure participant safety and sample homogeneity, exclusion criteria were operationally defined prior to recruitment. Severe cervical pathology was defined as cervical myelopathy, progressive cervical radiculopathy with neurological deficits, fracture, tumor, inflammatory cervical disease, severe cervical stenosis, or other red-flag conditions requiring medical management. All participants underwent a standardized clinical screening based on current neck pain clinical practice guidelines before enrollment. History of spinal surgery was defined as any previous cervical spine surgical procedure, including decompression, discectomy, fusion, arthroplasty, or stabilization surgery. Coagulation disorders included diagnosed bleeding disorders or conditions requiring special precautions for needling procedures [4,28-30]. Prior to enrollment, all participants will undergo a standardized screening examination performed by a physiotherapist and confirmed by a rehabilitation physician when necessary. Screening will include medical history, neurological examination, assessment of red flags for serious spinal pathology, and review of available imaging reports when clinically indicated (Textbox 1).

Textbox 1.Inclusion and exclusion criteria.
**Inclusion criteria**
Men and women aged 30-68 years.Chronic nonspecific neck pain lasting >3 months.Resting pain score ≥3 on the Numeric Pain Rating Scale.Not receiving other physical therapy treatment.Able to understand the study procedures and provide informed consent.
**Exclusion criteria**
Clinically significant sensory disorders or coagulation disorders.History of spinal surgery.Severe cardiac disease contraindicating electrical stimulationCentral or peripheral neurological disorders.Epilepsy.Needle phobia.Severe pathologies causing neck pain (eg, cervical stenosis, fracture, cervical spondylosis, tumors).Contraindications to transcutaneous electrical nerve stimulation.

Participants were not directly involved in the design or conduct of this trial. Feedback on the feasibility and acceptability of the intervention will be collected during follow-up to inform future research.

### Randomization, Treatment Allocation, and Adherence

Following the initial assessment, 70 patients with CNSNP will be randomly assigned to 1 of 2 groups: the experimental group receiving EDN plus specific therapeutic exercise or the control group receiving specific therapeutic exercise alone. EDN will be delivered by physiotherapists with formal postgraduate training in invasive physiotherapy and at least 3 years of clinical experience in ultrasound-guided EDN procedures.

During the study, participants will receive only the assigned intervention and will not be permitted to combine it with medications or other treatments. Any interference with the assigned treatment will result in study exclusion. Participants may withdraw from the study at any time, and the assigned interventions may be suspended or modified based on the evolution of symptoms (eg, adverse effects). All adverse events will be reported to the principal investigator, who will monitor affected patients and investigate potential causes.

To promote adherence, participants will be provided with a schedule card listing all treatment sessions, and weekly reminders will be sent via phone call, email, or WhatsApp.

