To minimize treatment variability, all therapists will follow a standardized intervention manual detailing patient positioning, trigger point identification, needle placement procedures, stimulation parameters, and safety precautions [31,32,35]. A treatment record form will be completed after each session documenting the muscles treated, number of needles inserted, stimulation intensity, treatment duration, and any adverse events.

Participants will be informed about the possibility of postneedling soreness and will be instructed to apply local cryotherapy if required during the first 48 hours. A follow-up telephone call will be conducted 48 hours after each treatment session to monitor adverse events and ensure participant safety.

Immediately after EDN, participants will perform the same cervical-specific therapeutic exercise program received by the control group. Therefore, this trial is designed to evaluate the added value of incorporating EDN into an exercise-based physiotherapy program rather than isolating the specific physiological effects of EDN itself.

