### Randomization

Participants will be randomly assigned to either the experimental group (EDN plus therapeutic exercise) or the control group (therapeutic exercise alone) using a computer-generated randomization sequence created by an independent statistician.

Allocation concealment will be ensured using sequentially numbered, opaque, sealed, tamper-evident envelopes prepared by an independent researcher not involved in participant recruitment, outcome assessment, or treatment administration. Envelopes will be opened sequentially only after completion of the baseline assessment and immediately before the first intervention session.

The outcome assessor will remain blinded to group allocation throughout the trial. Participants and treating physiotherapists cannot be blinded due to the nature of the interventions.

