### Data Analysis

Data will be analyzed using SPSS (version 28.0; IBM Corp) and will follow the intention-to-treat principle, whereby all randomized participants will be analyzed in the groups to which they were originally assigned, regardless of treatment adherence or completion. Additionally, a per-protocol analysis will be conducted including participants who complete at least 80% (5/6) of the in-person treatment sessions. All analyses will be conducted by a statistician blinded to group allocation.

Descriptive statistics will be calculated for all variables. Continuous variables will be presented as mean (SD) or median (IQR), depending on the data distribution, while categorical variables will be expressed as frequencies and percentages.

Baseline comparability between groups will be assessed using independent Student *t* tests for normally distributed continuous variables, Mann-Whitney *U* tests for nonnormally distributed variables, and chi-square tests for categorical variables. Normality will be evaluated using the Kolmogorov-Smirnov test and visual inspection of histograms.

A statistically significant group × time interaction will be interpreted as evidence of differential treatment effects over time. To evaluate the effects of the intervention over time and between groups, linear mixed-effects models will be used, including group (experimental vs control), time (baseline, postintervention, and 2-mo follow-up), and the group × time interaction as fixed effects, with participants included as random effects. This approach allows appropriate handling of repeated measures and missing data.

If model assumptions are not met, appropriate nonparametric alternatives (eg, Friedman test for within-group comparisons and Mann-Whitney *U* test for between-group comparisons with adjusted post hoc analyses) will be applied. Adjustment for multiple comparisons among secondary outcomes will be performed using the Holm-Bonferroni procedure.

Missing data will be handled using multiple imputation methods under the assumption of missing at random. Sensitivity analyses will be conducted to assess the robustness of the findings. Dropouts and losses to follow-up will be reported and compared between groups. Twenty imputed datasets will be generated using multiple imputation procedures.

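### Post-randomisation exclusion for medication or co-treatment conflicts with the promised intention-to-treat analysis, and what the exclusion ends is not defined

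*Protocol article*

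**What the plan says.** The section Randomization, Treatment Allocation, and Adherence states that "participants will receive only the assigned intervention and will not be permitted to combine it with medications or other treatments", and then that "Any interference with the assigned treatment will result in study exclusion". Both sentences govern the period after allocation and apply to both arms.

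The Data Analysis section commits to intention to treat: "all randomized participants will be analyzed in the groups to which they were originally assigned, regardless of treatment adherence or completion". It adds that "a per-protocol analysis will be conducted including participants who complete at least 80% (5/6) of the in-person treatment sessions", and on incomplete data that "Missing data will be handled using multiple imputation methods under the assumption of missing at random", with 20 imputed datasets. The primary end point is the between-group difference in NDI change from baseline to one day after the sixth session.

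On entry, Textbox 1 requires "Not receiving other physical therapy treatment", while the opening of the Participants section describes recruits more broadly, as people with no other current treatment of any kind.

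**The concern.** Taking a barred medication or treatment is behaviour after randomisation. One section excludes the participant for it; the other keeps everyone who was randomised. Both cannot be applied as written.

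The consequence depends on a term that the article leaves open. If study exclusion only stops the assigned sessions, the NDI is still measured and little is lost. If it ends outcome collection, the post-intervention NDI is missing for people selected by something likely to track their pain. If it ends inclusion in the analysis, the intention-to-treat statement is simply not met.

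The selection may also relate to arm. The Randomization section says "Participants and treating physiotherapists cannot be blinded due to the nature of the interventions", so a participant's decision to seek other treatment can be influenced by knowing the allocation. Detection may differ too: the statement that "A follow-up telephone call will be conducted 48 hours after each treatment session to monitor adverse events and ensure participant safety" appears only in the section on the electrical dry needling (EDN) arm. That section also advises cryotherapy for soreness without saying whether it counts as another treatment. At stake are the validity of the primary contrast and part of the attrition allowance, which was set for loss to follow-up only.

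**Working it through.** **1. Does another rule in the article absorb the exclusion?**
- *Per-protocol rule.* No. Treatment Schedule and Adherence Monitoring and Data Analysis both define that set by attendance alone (5 of 6 sessions). Co-treatment is not a criterion.
- *Stopping treatment.* Not clearly. The same paragraph deals separately with withdrawal and with suspending or modifying the intervention, and then uses a different term, exclusion from the study.
- *Adherence meaning attendance only.* This does not help, because the intention-to-treat sentence covers all randomised participants.
- *Multiple imputation.* Only nominally. It keeps the participant in the analysis set but replaces the outcome with a value informed by those still observed, most of whom would not have been excluded for co-treatment.

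**2. The plan's own sample size.** Inputs from Sample Size Calculation: difference 7.5, SD 10.58, two-sided 0.05, power 80%.
- n per arm = 2 × [10.58 × (1.960 + 0.842) / 7.5]² = 31.2, rounded up to 32. This reproduces the stated 32.
- 32 / 0.9 = 35.6, against the stated 35; close enough for this purpose.

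**3. Power if exclusions come on top of the planned loss.** The exclusion rates are assumptions; the article gives none. Noncentral t, standardised difference 7.5 / 10.58 = 0.709, complete cases, true difference held at 7.5.

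| Scenario | Control n | EDN n | Power |
|---|---|---|---|
| Planned 10% loss only | 35 × 0.9 = 31.5 | 31.5 | 0.791 |
| Plus 10% control, 5% EDN excluded | 31.5 × 0.90 = 28.4 | 31.5 × 0.95 = 29.9 | 0.758 |
| Plus 20% control, 5% EDN excluded | 31.5 × 0.80 = 25.2 | 29.9 | 0.730 |

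The cost is about 3 to 6 percentage points. Power depends on the two arm sizes, so swapping the rates between arms gives the same values. If 20% and 5% exclusions *were* the attrition rather than an addition to it, 35 × 0.80 = 28 and 35 × 0.95 = 33.25 would remain, with power about 0.78.

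**4. Possible shift in a completers-only estimate.** Let excluded participants be worse than retained ones in the same arm by a gap g (assumed 8 NDI points). Each arm's completer mean then looks better by p × g, so the contrast shifts by (p_control − p_EDN) × g.
- 10% v 5%: 0.05 × 8 = 0.4 points, or 0.4 / 7.5 = 5% of the target difference.
- 20% v 5%: 0.15 × 8 = 1.2 points, or 1.2 / 7.5 = 16%.
- Equal rates: 0.
- Rates reversed: same size, opposite sign.

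With more controls excluded, the apparent EDN benefit shrinks; with more EDN participants excluded, it grows.

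**5. Check by simulation.** Normal outcomes, SD 10.58, exclusion correlated 0.3 to 0.7 with poor NDI change, completers only.
- 5% EDN, 15% control excluded: benefit reduced by about 0.5 to 1.2 points.
- 15% EDN, 5% control: benefit inflated by about 0.5 to 1.2 points.
- 10% in each arm: about 0.
- Correlation 0: about 0 in every scenario.

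**The case against.** The strongest defence is that the rule is worded identically for both arms, that the article explicitly analyses everyone regardless of completion, and that it plans mixed models, multiple imputation and sensitivity analyses. On that reading, exclusion means only the end of the assigned treatment. This is possible, but the text does not say so, and an analysis method cannot restore an NDI that was not measured.

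Three stronger readings are tempting, and the documents do not support them.
- A reader might infer that outcome data are removed selectively by arm and that the primary contrast is therefore biased. No exclusion rates are given, and the bias may be near zero or of either sign. Unblinding and the EDN-section telephone call make differential exclusion a credible risk, not a documented fact.
- A reader might infer from Textbox 1 that analgesic users can be randomised and must then be excluded. The Participants section describes recruits as free of other current treatment. Whether that covers analgesics is not stated, so the supportable point is that the two entry descriptions differ in scope.
- A reader might take the 1.2-point shift as the error in the planned result. It is a completers-only figure under assumed rates and an assumed gap, whereas the plan uses mixed models and imputation. Those may not remove the bias, but the figure does not describe them.

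It can also be argued that using values observed after co-treatment is one choice of target, and that the effect without co-treatment is another. That is so, but the article's own intention-to-treat statement points to the first.

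Finally, Safety Considerations says analyses will not be modified once the first participant is registered, and data collection was expected to end by March 31, 2026. The first is no obstacle to carrying out an analysis already promised. The second limits what can be recovered.

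**Conclusion.** The conflict is real and touches the primary analysis: a stated post-randomisation exclusion stands against a stated analysis of all randomised participants, and neither the attendance-based per-protocol rule nor imputation resolves it. It should be fixed.

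The certain part is the contradiction and the undefined term. Bias is conditional: exclusion must end outcome collection or analysis, must be related to outcome in a way that missing at random does not capture, and must differ between arms in its frequency or in how strongly it selects on outcome. Under the assumed rates the size is modest: a loss of about 3 to 6 percentage points of power from 79%, and a completers-only shift of 0.4 to 1.2 NDI points if the gap is 8, with the sign undetermined.

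**What to change.** - Replace the exclusion sentence with wording that the deviation is recorded (type and date), NDI assessments continue on schedule, and the participant is analysed as randomised, with observed values, in the intention-to-treat analysis.
- If co-treated participants are to be removed anywhere, confine this to the per-protocol set, and amend its attendance-only definition in both Treatment Schedule and Adherence Monitoring and Data Analysis.
- Report co-treatment, and any exclusions already made, by arm. For those already excluded, use any NDI obtained and add a sensitivity analysis that departs from missing at random.
- Reconcile the scope of other treatment in the Participants section with that of other physical therapy in Textbox 1, and state whether the cryotherapy advised in the EDN section falls under the bar. Which co-treatments are permitted is a clinical matter on which no view is taken.

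**Cost.** A dated amendment before unblinding, a few sentences, one line on the case report form and one additional sensitivity analysis. No further participants or scheduled visits are needed. Because it delivers the intention-to-treat analysis already promised, it does not breach the no-modification statement in Safety Considerations. If the rule has already been applied and outcomes were not collected, those NDI values cannot be recovered, and this should be reported as a limitation.
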